### ***7.7.1 Requirements for Pregnancy Testing***

All WOCBP MUST have a negative pregnancy test within 72 hours as specified in Section 6.1 prior to receiving the investigational product. The minimum sensitivity of the pregnancy test must be 25 IU/L or equivalent units of HCG. If the pregnancy test is positive, the subject must not receive the investigational product and must not continue in the study.

Pregnancy testing must also be performed throughout the study as specified in Section 6.1 (see flow chart/time and events schedule) and the results of all pregnancy tests (positive or negative) recorded on the CRF or transferred electronically.

In addition, all WOCBP should be instructed to contact the investigator immediately if they suspect they might be pregnant (e.g., missed or late menstrual period) at any time during study participation.

### ***7.7.2 Reporting of Pregnancy***

If, following initiation of the investigational product, it is subsequently discovered that a study subject is pregnant or may have been pregnant at the time of investigational product exposure, including during at least

6 half-lives after product administration, the investigational product will be permanently discontinued in an appropriate manner (eg, dose tapering if necessary for subject safety). The investigator must immediately notify the Fondazione NIBIT/CRO of this event, record the pregnancy on the Pregnancy Surveillance Form (not an SAE form). Initial information on a pregnancy must be reported immediately to Fondazione NIBIT/CRO and the outcome information provided once the outcome is known. Completed Pregnancy Surveillance Forms must be forwarded to Fondazione NIBIT/CRO according to SAE reporting procedures described in Section 7.4.1.

Protocol-required procedures for study discontinuation and follow-up must be performed on the subject unless contraindicated by pregnancy (e.g., x-ray studies). Other appropriate pregnancy follow-up procedures should be considered if indicated. Follow-up information regarding the course of the pregnancy, including perinatal and neonatal outcome must be reported on the Pregnancy Surveillance Form.

Any pregnancy that occurs in a female partner of a male study participant should be reported to the sponsor. Information on this pregnancy will be collected on the Pregnancy Surveillance Form.

## **7.8 Other Safety Considerations**

Any significant worsening noted during interim or final physical examinations, electrocardiograms, x-rays, and any other potential safety assessments, whether or not these procedures are required by the protocol, should also be recorded on the appropriate non serious AE page of the CRF (paper or electronic) or SAE paper CRF page.

## **8 STATISTICAL CONSIDERATIONS**

### **8.1 Sample Size Determination**

The primary endpoint of the study will be the Maximum Tolerated Dose (MTD) and safety of the combination of SGI-110 plus ipilimumab.

Three patients will be treated at the first dose level for one cycle.

Dose escalation will be dependent on the available toxicity information (including adverse events that are not DLTs), PK, and efficacy information, as well as the recommendations from the scientific committee

The dose escalation of SGI-110 will follow a traditional 3+3 design Cohorts of 3-6 patients will receive a combination therapy of SGI-110 and Ipilimumab 3mg/kg. Each patient will receive SGI-110 sc. for 5 consecutive days (D1-5) during a 3-week cycle at one of the following doses:

- Dose Level -1: 15 mg/m^2 day
- Dose Level 0: 30 mg/m^2 day

- Dose Level +1: 45 mg/m^2 day
- Dose Level +2: 60 mg/m^2 day

In the absence of dose-limiting toxicities (DLTs), the starting dose of SGI-110 of 30 mg/m^2 day will be escalated to 45 mg/m^2 daily on Days 1-5. In the absence of DLT in the Dose Level +1, the dose of SGI-110 of 45 mg/m^2 day will be escalated to 60 mg/m^2 day on Days 1-5 (Level +2). In the presence of 1 DLT in 3 subjects of the single dose cohort, the cohort will enroll 3 more subjects at the same dose level. In the event that 2 or more DLTs were encountered at the single dose cohort, the previous lower dose level will be evaluated. The MTD will be the highest SGI-110 dose (15-60 mg/m^2 day on Days 1-5) level in combination with ipilimumab at which no more than 1 of 6 patients experiences a DLT. Once the MTD is established, additional subjects will be treated at that dose up to a total of 19 subjects in the entire study.

Time to events will be estimated using Kaplan-Meier Product Limit method, survival rates and median survival will be reported with their corresponding two-sided 95% confidence intervals for each arm and compared using a 2-tailed log-rank test.

Cox Proportional hazard model will be used to estimate Hazard Ratio and its 95% confidence interval and to adjust estimation for baseline prognostic factors.

Toxicity will be reported according to National Cancer Institute-Common Toxicity Criteria (NCI CTC) version 4.0 (2004) criteria. The safety analysis population will include all subjects who receive at least one dose of drug. Subjects will be assigned to treatment groups as treated. In tables showing the overall incidence of AEs, subjects who experienced the same event on more than one occasion are counted only once in the calculation of the event frequency.

All safety parameters will be summarized and presented in tables based on this safety population.

Demographic and baseline characteristics will be summarized for all treated subjects using descriptive statistics. Reporting of safety, extent of exposure, concomitant medications and discontinuation of study therapy will be based on all treated subjects. Worst toxicity grades per subject will be tabulated for AEs and on-study laboratory measurements by using the National Cancer Institute (NCI) Common Terminology Criteria for Adverse Events (CTCAE) version 4.0.

- Translational studies
- For a detailed work plan of translational studies see **Appendix A**

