Toxicity will be reported according to National Cancer Institute-Common Toxicity Criteria (NCI CTC) version 4.0 (2004) criteria. The safety analysis population will include all subjects who receive at least one dose of drug. Subjects will be assigned to treatment groups as treated. In tables showing the overall incidence of AEs, subjects who experienced the same event on more than one occasion are counted only once in the calculation of the event frequency.

All safety parameters will be summarized and presented in tables based on this safety population.

Demographic and baseline characteristics will be summarized for all randomized subjects using descriptive statistics. Reporting of safety, extent of exposure, concomitant medications and discontinuation of study therapy will be based on all treated subjects. Worst toxicity grades per subject will be tabulated for AEs and on-study laboratory measurements by using the National Cancer Institute (NCI) Common Terminology Criteria for Adverse Events (CTCAE) version 4.0.

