## **5.2 Method of Assigning Subjects to a Treatment**

After informed consent has been obtained, the patient will be enrolled into the study by a dedicated software, that will be available to the participant Center, and obtain a patient number. The exact procedures for using the dedicated software will be detailed in a separate document.

Following completion of all Screening Phase evaluation, and checking inclusion criteria site personnel will register the patient to obtain a treatment assignment (STEP2). The e-Clinical system assigns subjects to the SGI-110 dose level.

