#### 8.3.2.2 Immune-related Progression-free Survival (irPFS)

Immune-related progression free survival (irPFS) per irRC will be defined as the time between the date of randomization and the date of progression per irRC or death, whichever occurs first. A subject who dies without reported progression per irRC will be considered to have progressed on the date of death. For those subjects who remain alive and have not progressed, irPFS will be censored on the date of last evaluable TA. For those subjects who remain alive and have no recorded post baseline TA, irPFS will be censored on the day of last clinical evaluation.

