## 8.4 **Analyses**

### 8.4.1 *Demographics and Baseline Characteristics*

Demographic and baseline characteristics will be summarized for all subjects using descriptive statistics by treatment arms and overall for the FAS set. Categorical data will be presented as frequencies and percentages. For continuous data, mean, standard deviation, median, 25th and 75th percentiles, minimum and maximum will be reported.

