### 8.4.3 *Efficacy Analyses*

Analyses of efficacy endpoints will be based on all treated subjects (FAS set). The secondary efficacy endpoints will be evaluated with an explorative intent. The efficacy endpoints ir-DOR, ir-TTR will only be estimated for subjects with a confirmed best overall response of CR or PR. Exact two-sided 95% Confidence Intervals (CI) will be calculated using the binomial method for the proportion endpoints ir-DCR, ir-ORR.

OS will be estimated using Kaplan-Meier Product Limit method. A two-sided 95% confidence interval for the median survival will be computed using the Brookmeyer and Crowley method. PFS, ir-DOR, and Brain-PFS will be analyzed similarly.

OS will be further described using the survival rate, defined as the probability that a subject is alive at 6, 12, 18 and 24 months following date of the first treatment dose and estimated via the Kaplan-Meier method. A corresponding two-sided 95% confidence interval will be calculated.

Ir-TTR will be summarized using descriptive statistics.

A Cox regression analysis will be performed to adjust treatment effect for prognostic factors. Prognostic factors will be identified, before analysis, in the Statistical Analysis Plan.

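### Section 8 carries randomized-trial wording (log-rank test between arms, Cox treatment effect, irPFS from randomization) into a sequential, non-randomized 3+3 escalation

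*Combined protocol and SAP*

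**What the plan says.** **Design.** Section 8.1 states that "Cohorts of 3-6 patients will receive a combination therapy of SGI-110 and Ipilimumab 3mg/kg". Section 5.2 gives the allocation step: "The e-Clinical system assigns subjects to the SGI-110 dose level". Section 4.1.1 says the dose levels are worked through in sequence according to DLT incidence. The synopsis says that no formal sample size calculation was done and gives a range of 6 to 19 patients. Section 8.1 places the patients remaining after escalation at the MTD, up to 19 in all.

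**Analysis.**
- Section 8.1: Kaplan-Meier survival rates and medians are reported "for each arm and compared using a 2-tailed log-rank test". The next sentence adds a Cox hazard ratio with a 95% CI and does not say which groups it compares.
- Section 8.4.3: "A Cox regression analysis will be performed to adjust treatment effect for prognostic factors". The same section says "PFS, ir-DOR, and Brain-PFS will be analyzed similarly".
- Section 8.3.2.2: irPFS "will be defined as the time between the date of randomization and the date of progression per irRC or death".
- Synopsis, statistical methods: baseline characteristics are "summarized for all randomized subjects using descriptive statistics".
- Section 8.4.1: the same characteristics are shown "using descriptive statistics by treatment arms and overall for the FAS set".

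**The concern.** A log-rank test needs two groups, a Cox treatment effect needs a comparator, and a time-to-event endpoint needs a start date that each patient has. As written, the plan asks for all three in a study that supplies none of them explicitly. Whoever runs the analysis would have to decide what an arm is, what the hazard ratio contrasts and where irPFS begins, possibly after seeing data.

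The wording also bears on interpretation. Section 1.4.1 says the trial will determine the added benefit of SGI-110 on top of ipilimumab. A reported log-rank p-value or an adjusted treatment effect could be taken as evidence of that benefit, and a study in which everyone receives both drugs cannot provide it. irPFS is a named secondary objective (section 2.2), so its definition should be usable as it stands.

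**Working it through.** There is no power-based figure in the plan to reproduce: no alpha, effect size or event count is given for the log-rank test. The check is therefore mainly a comparison of the text with the design.

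**Step 1. Requirement against design**

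| Place | What the text requires | What the documents supply |
|---|---|---|
| 8.1, log-rank | Two or more arms | One combination at up to four SGI-110 dose levels; arm is not defined |
| 8.1, Cox hazard ratio | A named contrast | None named |
| 8.4.3, Cox | A treatment effect to adjust | No untreated or ipilimumab-only group |
| 8.3.2.2, irPFS | A randomization date | No randomization step; the system assigns the dose level (5.2) |
| Synopsis, baseline | A randomized set | Section 8.1 uses all treated subjects for the same table |
| 8.4.1, baseline | Treatment arms | Dose levels only |
| 8.4.3, Brain-PFS | An endpoint definition | Not in 2.2, 6.4.2 or 8.3 |

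The plan already contains usable alternatives. irTTR (8.3.2.1) and the survival rates (8.4.3) start at first dose. Section 8.4.3 also specifies single-group methods: Kaplan-Meier, Brookmeyer-Crowley intervals for the median and exact binomial intervals.

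**Step 2. If arm means dose level**

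The split between groups is an assumption, but both cases below can be reached under the protocol's rules with a total of 19:
- 3 versus 16: no DLT in 3 at Level 0, 2 or more in 3 at Level +1, return to Level 0, MTD declared there and expanded. Level 0 then has 19 − 3 = 16.
- 6 versus 13: as above, but Level +1 has 1 DLT in 3, is extended to 6 and then fails. Level 0 then has 19 − 6 = 13.

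In both cases the smaller group is the dose rejected for toxicity, and it was enrolled in a different period from the expansion group. Dose, calendar time and selection cannot be separated.

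*Interval width.* With an event in every patient, the 95% interval for the hazard ratio is the estimate multiplied and divided by exp(1.96 × √(1/n₁ + 1/n₀)).
- 3 versus 16: exp(1.96 × √(0.3333 + 0.0625)) = exp(1.233) = 3.43.
- 6 versus 13: exp(1.96 × √(0.1667 + 0.0769)) = exp(0.967) = 2.63.

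These are lower limits. Under the simulation below about 17 of 19 patients have an event. Scaling the variance by 19/17 gives exp(1.96 × √(0.3958 × 19/17)) = 3.68 and exp(1.96 × √(0.2436 × 19/17)) = 2.78.

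*Simulation.* Assumptions: exponential survival, median 10 months (section 1.3.6.2 reports 10.1 months for ipilimumab alone), follow-up uniform from 24 to 48 months (24 months' accrual and 24 months' follow-up, section 4.1.6), nominal two-sided 5% log-rank test, 10,000 trials per setting.
- 3 versus 16: type I error about 8%. Power for a two-fold hazard difference is 27% if the small group has the higher hazard and 13% if it has the lower.
- 6 versus 13: type I error about 6% to 7%, power about 20% to 29%.

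*Analytic check.* Schoenfeld power = Φ(√(d·p(1−p)) × |ln HR| − 1.96), with d = 19 events and HR 0.5 (|ln HR| = 0.693).
- 50/50: Φ(2.179 × 0.693 − 1.96) = Φ(−0.449) = 33%.
- 6:13: Φ(2.026 × 0.693 − 1.96) = Φ(−0.556) = 29%.
- 3:16: Φ(1.589 × 0.693 − 1.96) = Φ(−0.858) = 20%.

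For 80% power at HR 0.5 with equal groups, Schoenfeld gives (1.96 + 0.842)² / (0.25 × 0.480) ≈ 66 events. Freedman gives 9 × 7.85 ≈ 71. The study has at most 19 patients.

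**The case against.** The strongest reply is that this is leftover wording with little consequence. Most of that stands.
- The primary endpoint is MTD and safety (8.1, 8.3.1). No escalation, DLT or stopping rule uses a log-rank p-value or a hazard ratio. Section 8.4.3 declares the secondary efficacy endpoints explorative, and section 8.5 plans no interim efficacy analysis.
- Section 8.4.3 is largely right already: its main methods are single-group, and it contains no log-rank test. Its Cox sentence does remain.
- Section 8.1 speaks of treatment groups as treated, so dose level is a plausible meaning of arm. The plan does not say so, and this reading cannot supply a randomization date.
- Patients enter treatment within 3 days of eligibility (4.1.1), and the first on-study tumor assessment is at week 12 (4.1.2). Any plausible origin for irPFS, registration or first dose, should differ by only days.
- A Cox model of prognostic factors with no treatment term is possible in one group, although at most 19 patients would limit it severely. The text asks for something else.

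A reader might infer that these analyses estimate nothing at all, or that the trial's conclusions are compromised. The documents do not support that. A dose-level contrast can be computed; it is confounded and imprecise, but the plan does not make it confirmatory. The dose-level figures also rest on assumed splits and an assumed median. They describe one possible reading, while the defect itself lies in the text.

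**Conclusion.** The point holds as an inconsistency in current text, and it should be corrected before analysis. The between-arm log-rank test, the Cox contrast and the randomization origin are stated rules that this design cannot carry out as written. Brain-PFS has no definition.

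The practical size is moderate. MTD and safety results are unaffected, and the irPFS values would probably move by only days. The main risk is a p-value or hazard ratio that looks like an efficacy comparison. On the dose-level reading it would come from a test with inflated type I error and low power, and from an interval more than three-fold in each direction for a 3 versus 16 split. Those figures assume exponential survival with a 10-month median and all 19 places filled. The textual contradiction depends on none of these assumptions.

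**What to change.** 1. Section 8.3.2.2: define irPFS from the date of first dose, matching irTTR and the survival rates.
2. Section 8.1: delete the between-arm log-rank comparison and the Cox hazard ratio sentence. Section 8.4.3: delete the Cox treatment-effect sentence. Any display by dose level should be descriptive, without a test.
3. Section 8.4.3: delete Brain-PFS.
4. Synopsis: replace the randomized set with all treated subjects, as in section 8.1. Section 8.4.1: replace treatment arms with dose level.
5. Report Kaplan-Meier estimates with 95% CIs for the FAS. A separate summary of patients treated at the MTD is optional.

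The cost is a wording amendment to the protocol and SAP. It needs no new data, changes no dose or clinical rule, and reduces the analysis work.

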## **8.2 Populations for Analyses**

All treated subjects: All subjects who received at least one dose of SGI-110 and ipilimumab. (Full Analysis Population-FAS).

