## **5 TREATMENTS**

### **5.1 Study Treatment**

All protocol-specified investigational and non-investigational products are considered study drug.

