### ***5.2.1 Dosage and Administration***

#### ***SGI-110 schedule***

SGI-110 will be administered:

Start at 30 mg/m^2 day s.c. on W0, 3, 6, 9 Day 1 - 5 q21 days. Dose Level -1: 15 mg/m^2 day; dose level +1: 45 mg/m^2 day, Dose Level +2: 60 mg/m^2 day for a total of 4 cycles.

SGI-110 is administered by SC injection preferably in the abdominal area; however the thigh and arms may be used. A Luer-Lok disposable syringe should be used when dispensing and administering SGI-110. Due to the slightly viscous nature of the preparation, use of thin-walled subcutaneous needle is highly recommended for ease of subcutaneous administration and subject comfort. SGI-110 should be injected slowly (up to one minute) as some injection site discomfort or pain may be experienced.

If injection site pain is reported upon injection, apply ice packs to the injection site both before and after injection. If the injection site events are reported at subsequent injections despite slow injection and the use of ice packs, pre-treatment with topical or systemic analgesics can be considered. The total amount (in mg) of SGI-110 to be administered will be determined based on the body surface area (BSA). In calculating the BSA, actual heights and weights taken at enrolment should be used. There will be no adjustments to “ideal” body weight or dose modifications related to changes in body weight < +/- 10%. The institutional standard for calculating BSA is acceptable.

The site(s) of SGI-110 SC injections will be captured on the dosing CRF.

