## **6.3 Safety Assessments**

Data for the procedures and assessments specified in this protocol should be submitted to Fondazione NIBIT/CRO on a case report form. Additional procedures and assessments may be performed as part of standard of care; however, data for these assessments should remain in the subject's medical record and should not be provided to Fondazione NIBIT/CRO, unless specifically requested.

All subjects who receive at least 1 dose of study drug will be evaluable for safety parameters. Additionally, any occurrence of non-SAE or SAE from time of consent forward, up to and including follow-up visits, will be reported. See Section 7: Adverse Event Reporting.

The visits will occur on every treatment day and also on Day 8, for all cycles, on Day 8,15 for the first cycle. There is a 30-day (+ 5 day) safety visit after the last study treatment in this study.

Safety will be evaluated for all treated subjects using the NCI CTCAE version 4.0. Safety assessments will be based on medical review of AE reports and the results of vital sign measurements, physical examinations and clinical laboratory tests. The incidence of AEs will be tabulated and reviewed for potential significance and clinical importance.

Safety monitoring will be performed on an on-going basis as described in Section 4.1.3.

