### 8.4.2 *Safety Analyses*

Reporting of safety, extent of exposure, concomitant medications and discontinuation of study therapy will be based on all treated subjects; for on-study laboratory test results, all treated subjects with at least one on-study laboratory measurement available will be included in the analysis. The reporting period for safety data will be from the date of first dose received on this study to 70 days (5 half-lives) after the last dose is received. Serious adverse events are reported from the time of consent forward for all subjects.

The analysis of safety will be based on the frequency of AEs and their severity for all treated subjects. Worst toxicity grades per subject will be tabulated for AEs and on-study laboratory measurements by using the NCI CTCAE version 4.0. Additionally, immune-related (ir) see Section 1.3.5.3, drug-related and serious AEs will be tabulated separately, and listings by subject will be produced for all deaths, all SAEs and all AEs leading to discontinuation of study drug.

Assessment of extent of exposure will include tabulation of dose omissions, reductions and delays.

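### The full analysis set requires a dose of both drugs, so SGI-110-only patients leave the efficacy analyses, and the plan contradicts itself on whether they count for safety

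*Combined protocol and SAP*

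**What the plan says.** **The set.** Section 8.2 has one entry, all treated subjects, also labelled the full analysis set: "All subjects who received at least one dose of SGI-110 and ipilimumab".

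**Efficacy.** Section 8.4.3 uses it directly: "Analyses of efficacy endpoints will be based on all treated subjects (FAS set"). Section 8.3.2.1 defines irDCR and irORR as proportions of treated subjects. Section 8.4.3 measures survival rates from the first treatment dose. Section 8.4.1 also describes baseline data on the FAS.

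**Safety.** Two rules appear.
- Section 8.1 says "The safety analysis population will include all subjects who receive at least one dose of drug", and then "All safety parameters will be summarized and presented in tables based on this safety population". The statistical part of the synopsis says the same. Section 6.3 agrees: "All subjects who receive at least 1 dose of study drug will be evaluable for safety parameters". Section 5.1 makes clear that either product qualifies: "All protocol-specified investigational and non-investigational products are considered study drug".
- Section 8.4.2 says "The analysis of safety will be based on the frequency of AEs and their severity for all treated subjects". Section 8.1 also bases safety, exposure and discontinuation reporting on all treated subjects, shortly after defining the one-dose population.

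**Timing.** Section 5.2.1 schedules SGI-110 "on W0, 3, 6, 9 Day 1 - 5 q21 days" and ipilimumab at Weeks 1, 4, 7 and 10. Section 4.1.1 and the section 6.1 flow chart agree. The study design part of the synopsis and the study schema (4.1.4) instead put ipilimumab on Day 1 of each three-week cycle.

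**MTD.** Section 8.3.1 bases the MTD on a DLT evaluable population. No section defines it.

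**The concern.** Under the Week 0 / Week 1 schedule, the first five-day SGI-110 course is finished before ipilimumab begins. Read literally, section 8.2 then makes membership of the FAS depend on what happens to a patient after treatment has started. A patient who stops for toxicity, withdraws or dies in that interval has been exposed to study drug but is not an all treated subject.

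Three things are at stake. The response and disease-control denominators lose patients who are very unlikely to be in the numerators. Survival counted from first dose can include no death before the first ipilimumab dose, because a patient who dies in that interval is not in the set. And for safety, which the plan makes part of the primary endpoint, a reader cannot tell which denominator the tables will use.

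**Working it through.** **Step 1. Who is in which set.** Take a patient who receives SGI-110 in Week 0 and never receives ipilimumab.

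| Place in the plan | Rule | Is the patient included? |
|---|---|---|
| 8.2, FAS | both drugs | no |
| 8.4.3, efficacy | FAS | no |
| 8.1 and synopsis, safety population | one dose of drug | yes |
| 6.3 with 5.1, evaluable for safety | one dose of either product | yes |
| 8.1 and 8.4.2, safety reporting | all treated subjects | no, if the label has its 8.2 meaning |
| 8.3.1, MTD | DLT evaluable population | cannot be determined |

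For efficacy there is one rule, and no other section repairs it. For safety there are two incompatible rules.

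**Step 2. Size of the efficacy shift.** The plan gives no figure to reproduce: the sample size of 6 to 19 is not calculated, and no rate of early loss is stated. The counts below are therefore assumptions. With x patients achieving the endpoint among n treated, and k excluded patients none of whom achieved it, the reported rate is x/(n − k) instead of x/n, a ratio of n/(n − k). The intervals are exact binomial, as section 8.4.3 specifies: lower limit Beta(0.025; x, n − x + 1), upper limit Beta(0.975; x + 1, n − x).

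| Endpoint (assumed) | All 19 kept | Excluded | Reported |
|---|---|---|---|
| irDCR, x = 6 | 6/19 = 31.6% (12.6 to 56.6) | 2 | 6/17 = 35.3% (14.2 to 61.7) |
| irORR, x = 3 | 3/19 = 15.8% (3.4 to 39.6) | 2 | 3/17 = 17.6% (3.8 to 43.4) |
| irDCR, x = 8 | 8/19 = 42.1% (20.3 to 66.5) | 1 | 8/18 = 44.4% (21.5 to 69.2) |
| irDCR, x = 8 | as above | 2 | 8/17 = 47.1% (23.0 to 72.2) |
| irDCR, x = 8 | as above | 3 | 8/16 = 50.0% (24.7 to 75.3) |

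In the first row the shift is 35.3 − 31.6 = 3.7 points, against an interval 56.6 − 12.6 = 44.0 points wide. The exception is a patient who stops after SGI-110 alone and still has disease control. Excluding one such patient gives 5/18 = 27.8%, a shift downward.

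**Step 3. How likely any exclusion is.** If each patient independently has probability p of never reaching ipilimumab, the chance that at least one of 19 is excluded is 1 − (1 − p)^19. For assumed p of 2%, 5% and 10% this is 32%, 62% and 86%.

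**Step 4. What the safety contradiction is worth.** Suppose 6 of 19 treated patients have a severe adverse event, 31.6% (assumption). Under the one-dose rule the table shows 6/19. If the 8.2 meaning is carried into 8.4.2, and 1, 2 or 3 of those six received SGI-110 only, the table shows 5/18 = 27.8%, 4/17 = 23.5% or 3/16 = 18.8%. The documents do not say which rule prevails.

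**The case against.** **The safety data are not settled as lost.** A reader might infer that SGI-110-only patients drop out of the safety tables and that toxicity is understated, so that 1/6 with serious toxicity in a cohort becomes 0/5. The documents do not support this. Section 8.1 and the synopsis promise all safety tables on the one-dose population. Section 8.4.2 reports serious events from consent for all subjects and lists every death and serious event. The safety committee reviews all adverse events (4.1.3). This part of the objection stands: for safety the finding is a contradiction.

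**Exclusion after an early DLT is not forced.** A reader might also infer that a Week 0 DLT automatically removes a patient, because section 4.2.3 lists DLT as a reason to discontinue. The note in that section allows the other drug to continue when the event is attributable to only one of the two, and section 5.3.1 allows SGI-110 to resume after a myelosuppressive DLT. Exclusion is therefore possible, not certain. Some DLT criteria also need days to weeks to be met, and the first on-study tumor assessment is at Week 12, so few exclusions would rest on a documented early DLT or progression.

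**The MTD is not affected through the FAS.** Section 8.3.1 uses a separate population. This stands, although that population is undefined.

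**The effect is small and efficacy is exploratory.** Both are true. The lead-in is about a week against survival rates at 6 to 24 months, and a numerator of zero, the only irDCR trigger for terminating the study, stays zero with either denominator.

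**The wording may only mean any study treatment.** It may, but the plan has a term that covers either product, defined in 5.1 and used in 6.3, and section 8.2 does not use it.

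What survives is the efficacy definition and the conflict over the safety population.

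**Conclusion.** The point holds for efficacy and, as a contradiction, for safety. Read literally, the only set listed in section 8.2 leaves SGI-110-only patients out of all efficacy analyses. The resulting bias in irDCR and irORR is upward apart from rare exceptions, and modest: 3.7 points for irDCR in the example with 2 of 19 excluded. Survival from first dose is conditioned on reaching the first ipilimumab dose. For safety, the plan gives two incompatible populations for part of its primary endpoint.

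This rests on the literal reading of section 8.2 and on the Week 0 / Week 1 schedule. If both drugs start on Day 1, as the synopsis design text and the study schema have it, the one-week gap disappears. All counts and loss rates above are assumptions. The documents do not support a claim that safety data will be lost, that early DLTs force exclusion, or that dose decisions are biased by the FAS.

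**What to change.** 1. In section 8.2, define all treated subjects, serving as both FAS and safety set, as subjects who received at least one dose of SGI-110 or ipilimumab.
2. Use that definition in section 8.1 and in 8.4.1 to 8.4.3, and align the synopsis, so that each table has one stated denominator.
3. Have the sponsor define the DLT-evaluable population of section 8.3.1 separately, stating how a patient with a DLT before ipilimumab is handled. It should not be assumed to carry a both-drugs rule.
4. Reconcile the passages that give ipilimumab on Day 1 (synopsis study design, 4.1.4) with those that give Week 1 (4.1.1, 5.2.1, 6.1).

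Items 1 and 2 need a few sentences and no new data. Their only statistical cost is a denominator that may be slightly larger, and so slightly lower efficacy rates. Item 3 adds one definition. Item 4 is a correction of text that is needed in any case.
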